## Abstract

The optimal timing of surgery and the number of courses of perioperative chemotherapy for high-risk soft tissue sarcoma patients are still controversial. Tumour growth during neoadjuvant chemotherapy led to limb amputation in some patients. This study aims to confirm the non-inferiority of surgery and three courses of adjuvant chemotherapy with adriamycin (30 mg/m^2^, days 1 and 2) plus ifosfamide (2 g/m^2^, days 1–5) compared with our standard treatment of three courses of neoadjuvant chemotherapy and surgery followed by two courses of adjuvant chemotherapy with adriamycin plus ifosfamide for localized high-risk soft tissue sarcoma patients. This is a multi-center, two-arm, open-label, randomized phase III trial. The primary aim is to confirm the non-inferiority in overall survival (margin: hazard ratio of 1.61). This is the first randomized controlled trial to compare neoadjuvant chemotherapy and immediate surgery for soft tissue sarcoma. This trial was initiated on 16 November 2022 and registered with the Japan Clinical Trials Registry (jRCTs031220446).

## Introduction

Soft tissue sarcomas (STSs) are rare malignant tumours of mesenchymal origin that arise from all body soft tissues, including fibrous, adipose, muscular and vascular tissues. It accounts for ~1% of all malignant tumours and is one of the most common rare cancers. According to the SEER (Surveillance Epidemiology and End Results) Database, STS accounted for 48 012 (1.5%) of the 3.11 million malignancies registered in the USA (1).

The standard treatment of stage I and II non-round cell STS is surgery alone. The 5-year survival proportion is ~95% for stage I and ~80% for stage II (2, 3). For stage III cases with superficial lesions, surgery alone is still considered the standard treatment since the 5-year survival proportion is ~70% or more. On the other hand, the 5-year survival proportion for stage III patients with deep lesions, which are located deeper than the superficial fascia, is poor at ~50% if treated with surgery alone, so perioperative chemotherapy is often used in addition to surgery (2, 4, 5). In recent clinical trials, perioperative chemotherapy with adriamycin (ADM) or other anthracycline, plus ifosfamide (IFO), has been employed for ‘high-risk’ cases, such as high-grade, >5 cm in diameter and deep-seated (6–10). A meta-analysis of 18 trials revealed a significant increase in overall survival (OS) with ADM plus IFO (AI)–based perioperative chemotherapy (11). So far, there are 10 papers on clinical trials of perioperative chemotherapy with AI regimen, although the doses, timing of administration and number of courses have not been standardized (Table 1).

**Table 1 TB1:** Summary of clinical trials of perioperative adjuvant chemotherapy with adriamycin plus ifosfamide for localized soft tissue sarcoma

Author	Year	Study type	*N*	5y-OS	5y-PFS	NAC/AC	Dose	Course
JCOG0304 (6)	2015	Single arm	70	82.6	63.8	NAC + AC	A 300/I 50	5(3 + 2)
JCOG1306 (7)	2022	RCT	70	91.4^a^	73.5^a^	NAC + AC	A 300/I 50	5(3 + 2)
Gortzak E (12)	2001	RCT	67	65	56	NAC	A 150/I 15	3
Gronchi A (8)	2012	RCT	161	71	61.1	NAC + AC	E 600/I 45	5(3 + 2)
			160	68	61.4	NAC	E 360/I 27	3
Gronchi A (9)	2017	RCT	144	89^a^	62^a^	NAC	E 360/I 27	3
Brodowicz T (13)	2000	RCT	31	88.1	70.8	AC	A 300/I 36	6
Frustaci S (4)	2001	RCT	53	69^a^	50^a^	AC	E 300/I 45	5
Petrioli R (14)	2002	RCT	45	72	69	AC	E 300/I 24	4
Woll PJ (10)	2012	RCT	175	67.8	54.9	AC	E 375/I 25	5
Schliemann C (15)	2018	Single arm	104	75.6	61.2	AC	A 300/ I 20	4

RCT, randomized controlled trial; OS, overall survival; PFS, progression-free survival; A, ADM (mg); I, IFO (g); E, epirubicin (mg).

^a^Percentage of survival at 46–48 months.

The Bone and Soft Tissue Tumor Study Group (BSTTSG) of the Japan Clinical Oncology Group (JCOG) conducted JCOG0304 and the subsequent JCOG1306 trials in Japan to establish the standard treatment for stage III high-risk STS patients. JCOG0304 evaluated the efficacy and safety of a treatment regimen of pre-operative and post-operative AI. That trial showed a good 5-year OS of 82.6% and 5-year progression-free survival (PFS) of 63.8% in patients at high risk (6), establishing three courses of neoadjuvant chemotherapy (NAC) followed by surgery and two courses of adjuvant chemotherapy (AC) with AI as the standard treatment. However, the primary tumour became a progressive disease (PD) according to the revised Response Evaluation Criteria in Solid Tumours (RECIST) guidelines during NAC in 4.3%, and 21% of patients discontinued chemotherapy due to toxicity or patient refusal. This result highlighted the risk of PD during NAC and their high toxicity. In this context, a phase III trial of AI versus gemcitabine plus docetaxel (GD) (JCOG1306) was conducted to confirm the non-inferiority of GD against AI. That trial failed to show the non-inferiority of GD against AI (7). Consequently, three courses of NAC with AI followed by surgery and two courses of AC with AI are considered the standard treatment for stage III high-risk STS patients. That trial also revealed that only 1.4% of the patients showed partial response (PR), whereas 8.6% presented PD during NAC, according to the RECIST guidelines (6,7). As a result, of the 65 patients deemed eligible for limb-sparing surgery at study enrolment, three (4.6%) underwent limb-amputation surgery after NAC. In these cases, limb sparing was possible if surgery was immediately performed after enrolment. Thus, the study revealed the potential disadvantage of NAC: it may cause unnecessary amputation for some patients. Immediate surgery followed by AC may avoid the risk of extended resection due to tumour growth in cases where chemotherapy is ineffective.

Toxicity with AI treatment is also a concern. The most common adverse events are hematologic toxicity, with grade 3/4 leucopoenia and neutropenia almost inevitable, and grade 3/4 non-hematologic toxicity with nausea and anorexia is also common. Given the severe toxicity, a randomized controlled trial (RCT) of three courses of NAC followed by surgery and two courses of AC versus three courses of NAC followed by surgery was recently conducted in Europe (8). The results showed that the 5-year OS was 71% (95% CI: 63–77%) in the former arm compared with 68% (95% CI: 60–75%) in the latter arm, with a hazard ratio (HR) of 1.00 (90% CI: 0.72–1.39), proving non-inferiority in OS. Regarding toxicity, renal dysfunction occurred in 1.5% of patients receiving five courses of chemotherapy but not in those receiving three courses. The incidence of hematologic toxicity also increased with two additional courses, again suggesting that an increase in the number of courses is associated with an increase in toxicity. However, the rationale for using three courses of NAC as the test treatment was not stated in that paper. Globally, there is no evidence of whether chemotherapy or surgery should be performed first. Surgery after NAC is the standard treatment in some countries including Japan and Italy, but other countries and physicians consider resection as the first treatment, with chemotherapy as an option or post-operative consideration. Indeed, in a recently reported clinical trial in Germany for STS, resection was followed by chemotherapy (15).

The National Comprehensive Cancer Network (NCCN) guidelines make no recommendations regarding optimal resection timing or number of courses since there is no evidence (16). The ESMO Clinical Practice Guidelines state that perioperative adjuvant chemotherapy for STSs is a treatment option for high-risk patients. They also mention that three courses of NAC with AI may be effective but do not address the superiority of NAC over AC (17).

The current clinical challenge in this field is to optimize the balance between the survival benefit of perioperative chemotherapy with AI and the toxicity and risk of extended surgery. From this viewpoint, the immediate surgery followed by three courses of AC is expected to be an effective and safer treatment since it will avoid the risk of extended resection due to tumour growth during NAC and reduce the number of chemotherapy courses. We, therefore, designed a randomized phase III trial of Neo-adjuvant and adjuvant chemotherapy vs. Adjuvant Chemotherapy for LocalizEd Soft tissue Sarcoma (NACLESS trial) to confirm the non-inferiority of three courses of AC with AI compared with three courses of NAC and two courses of AC with AI for localized high-risk STS patients for establishing a better standard treatment.

## Patients and Methods

### Study design

This is a multi-centre, randomized, open-label, parallel-arm, phase III trial. Initially, this trial is conducted at 37 centres in Japan, all of which are participating in the JCOG BSTTSG. This trial aims to confirm non-inferiority in OS of immediate surgery followed by three courses of AC compared with the standard treatment of three courses of NAC plus surgery plus two courses of AC in patients with high-risk localized STS. Patients who meet all the following eligibility criteria and none of the exclusion criteria are eligible for enrolment (Table 2). The study protocol was approved by the National Cancer Center Hospital Certified Review Board for Clinical Trials (Certification No. CRB3180008) before initiating patient accrual.

**Table 2 TB2:** Summary of inclusion and exclusion criteria of JCOG2102

Inclusion criteria	Exclusion criteria
(1) Grade 2 or 3 (FNCLCC histological grading system) non-round cell soft-tissue sarcoma with histology of undifferentiated sarcoma (pleomorphic, spindle cell), adult fibrosarcoma, myxofibrosarcoma, leiomyosarcoma, synovial sarcoma, liposarcoma (dedifferentiated, myxoid, pleomorphic), pleomorphic rhabdomyosarcoma, malignant peripheral nerve sheath tumour, angiosarcoma (WHO classification 2020) diagnosed by open biopsy specimen (2) 10 or more unstained tumour tissue slides are available (3) Primary tumour (4) Tumour in the extremities or trunk (5) T2-4N0M0 (UICC/AJCC, 8th edition) and deeply seated (localized deeper than the investing fascia, invades the investing fascia or penetrates the investing fascia) according to the latest imaging studies (6) Having measurable lesion on MRI axial section (7) Resectable with a marginal or wide margin (8) Age between 16 and 70 years (9) ECOG performance status (PS) of 0–1 (10) No history of chemotherapy nor radiation therapy for any cancer including non-round cell STS (11) All of the following are met for the most recent laboratory findings within 14 days prior to enrolment: (i) Neutrophil count ≥1500/mm^3^ (ii) Haemoglobin ≥8.0 g/dl (No blood transfusion within 14 days prior to the test used for registration) (iii) Platelet count ≥100 000/mm^3^ (iv) Total bilirubin ≤1.5 mg/dl (v) AST ≤ 100 U/L (vi) ALT ≤100 U/L (vii) Serum creatinine ≤1.5 mg/dl (viii) Creatinine clearance ≥60 ml/min (12) The latest ECG within 35 days prior to enrolment shows normal or no changes requiring treatment (13) Written informed consent	(1) Synchronous or metachronous (within 5 years) malignancies except cancer with 5-year relative survival proportion of 95% or more (2) Active infection requiring systemic therapy (3) Febrile more than 38°C (4) Women (possibly) in pregnancy, within 28 days post-partum, or breastfeeding. Men who wish to get their partner pregnant (5) Patients with psychiatric disorders or psychiatric symptoms (6) Patients requiring systemic steroid medication (7) Poorly controlled diabetes mellitus or routine administration of insulin (8) Poorly controlled hypertension (9) Unstable angina within 3 weeks or with a history of myocardial infarction (10) Poorly controlled valvular disease, dilated cardiomyopathy or hypertrophic cardiomyopathy (11) Positive HBs antigen

FNCLCC, Fédération Nationale des Centre de Lutte Contre le Cancer; ECOG, Eastern Cooperative Oncology Group; ECG, electrocardiogram.

### Interventions

Patients will be randomized to arm A or B (Fig. 1) at the JCOG Data Center. Arm A will receive standard treatment (three courses of NAC, surgery and two of AC) and arm B will receive trial treatment (surgery and three courses of AC), with AI comprising adriamycin (30 mg/m^2^, days 1, 2) and ifosfamide (2 g/m^2^, days 1–5).

**Figure 1 f1:**
[figure not shown]
Flowchart of JCOG2102 (Neo-adjuvant and adjuvant chemotherapy vs. Adjuvant Chemotherapy for LocalizEd Soft tissue Sarcoma) study.

Random allocation will be based on a minimization method that adjusts for (i) the centre, (ii) histological grade (Grade 2 vs. Grade 3), and (iii) T-classification (T2 vs. T3–4). Detailed procedures for random allocation are not given to participating institutes and investigators.

### Outcomes

The primary endpoint is OS, defined as the period from the date of enrolment until the date of death from any cause. Secondary endpoints are PFS, the response rate of NAC, the pathological response rate of NAC, the proportion of reduction surgery, the proportion of extended surgery, post-operative limb function (extremities), the proportion of limb salvage, adverse events and serious adverse events. PFS is defined as the period from the date of enrolment until the date of progression or death from any cause, whichever is earlier. Progression in this trial includes both PD according to the revised Response Evaluation Criteria in Solid Tumours (RECIST) guidelines and clinical disease progression not confirmed by imaging studies. The response rate of NAC is defined as the proportion of all eligible patients in arm A who are classified as ‘CR’ or ‘PR’ by RECIST. The proportion of reduction surgery is defined as the proportion of patients out of all enrolled cases whose actual surgery is reduced compared with the surgery planned at enrolment. The proportion of extended surgery is defined as the proportion of patients out of all enrolled cases whose actual surgery is extended compared with the surgery planned at enrolment. Post-operative limb function is assessed by the International Society of Limb Salvage score. The proportion of limb salvage is defined as the proportion of affected limbs that could be preserved after surgery, with the denominator being all limb-occurring cases enrolled.

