### Participant timeline

The participant timeline is summarized in Table 3. Candidates who agree to participate are checked for eligibility based on the inclusion/exclusion criteria, and enrolment is completed after confirmation of eligibility. Physical examination, Eastern Cooperative Oncology Group performance status (PS), body weight, body height, complete blood count (CBC), serum biochemistry, urine analyses, creatinine clearance, chest X-ray and percutaneous saturation of oxygen (SpO_2_) are performed within 14 days before registration. Electrocardiography, computed tomography (CT) of the chest, magnetic resonance imaging (MRI) of the primary site and additional CT/MRI of the associated lymph nodes area are performed within 35 days before registration. Tests of hepatitis and 18-fluorodeoxyglucose positron emission tomography–computed tomography (PET-CT) or bone scintigraphy should also be performed before registration. Participants should commence the treatment protocol within 7 days (arm A) or 28 days (arm B) of registration.

**Table 3 TB3:** The study schedule

Arm A	Enrolment	NAC			Surgery		AC		Follow-up
		1	2	3	Before	After	1	2	
Informed consent	○	◯							
Inclusion/exclusion criteria	◯								
Physical examination	○	○	○	○	○	○	○	○	○
Body weight	○	○	○	○	○		○	○	
Height	○								
PS	○	○	○	○	○		○	○	
Blood examinations^a^	○	○	○	○	○		○	○	○
Urine analysis	○		○	○			○	○	
Creatinine clearance	○								
HBs-Ag, HBc-Ab, HBs-Ab, HCV-Ab	○								
Chest X-ray	○		○	○	○		○	○	○
Chest CT	○				○				○
MRI of primary site	○				○				○
CT/MRI for lymph nodes	○								
PET-CT/Bone scintigraphy	○								
SpO_2_	○		○	○			○	○	
ECG	○				○				
Adverse events		○	○	○	○	○	○	○	○
Arm B	Enrolment	Surgery		AC			Follow-up		
		Before	After	1	2	3			
Informed consent	○								
Inclusion/exclusion criteria	◯								
Physical examination	○		○	○	○	○	○		
Body weight	○								
Height	○								
PS	○			○	○	○			
Blood examinations^a^	○	○		○	○	○	○		
Urine analysis	○			○	○	○			
Creatinine clearance	○								
HBs-Ag, HBc-Ab, HBs-Ab, HBC-Ab	○								
Chest X-ray	○			○	○	○	○		
Chest CT	○						○		
MRI of primary site	○						○		
CT/MRI for lymph nodes	○								
PET-CT/Bone scintigraphy	○								
SpO_2_	○			○	○	○			
ECG	○								
Adverse events			○	○	○	○	○		

^a^CBC, serum biochemistry. PS, Performance Status; SpO_2_, percutaneous oxygen saturation; ECG, electrocardiogram.

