The criteria for dose reduction or discontinuation are set as follows. In the event of severe myelosuppression, liver dysfunction, diarrhoea, oral mucositis or infection, the dose is reduced by 20% per step in the next course. Further chemotherapy should be terminated if the dose reduction criteria are still met after two steps of dose reduction.

In the event of severe pneumonitis, increased creatinine, arrhythmia, cardiac dysfunction, vertigo, nervous system disorder or haematuria, the chemotherapy should also be discontinued. No other anti-cancer drugs, hormone therapies other than steroids, radiotherapy or immunotherapy should be used during protocol treatment.

In arm A, if any of the following (i–iv) are met after the start of NAC, subsequent chemotherapy should be discontinued: (i) exacerbation of disease after the start of protocol treatment; (ii) the protocol treatment cannot be continued due to adverse events including Grade 4 non-hematologic toxicity and delay of >14 days of the start of the following course; (iii) the patient requests termination of protocol treatment for reasons related to adverse events; and (iv) the patient requests termination of protocol treatment for reasons unrelated to adverse events. In case of discontinuation of NAC, protocol treatment is continued, and surgery is performed after determining tumour reduction efficacy as far as possible. However, AC is not given, and protocol treatment is discontinued upon completion of surgical treatment. Protocol treatment should be discontinued if any of the following (i–vi) are met: (i) progression of disease; (ii) the protocol treatment cannot be continued due to adverse events including Grade 4 non-hematologic toxicity; (iii) the patient requests termination of protocol treatment for reasons related to adverse events; (iv) the patient requests termination of protocol treatment for reasons unrelated to adverse events; (v) death during protocol treatment; and (vi) post-enrolment exacerbation prior to the initiation of protocol treatment (inability to start the protocol treatment due to rapid progression), the discovery of protocol violation, change of treatment due to a change in the pathological diagnosis after enrolment, or other reasons that make the patient ineligible for protocol treatment.

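### PFS counts RECIST growth of the unresected primary during neoadjuvant chemotherapy, to which arm B is only briefly exposed; the between-arm PFS comparison tends to favour arm B and needs a prespecified companion analysis

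*Protocol article*

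**What the plan says.** All references are to the protocol article.

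- **Outcomes.** PFS is a secondary endpoint that starts at enrolment in both arms and ends at progression or death. On what counts as an event, the article says: "Progression in this trial includes both PD according to the revised Response Evaluation Criteria in Solid Tumours (RECIST) guidelines". Clinical progression without imaging confirmation counts as well. No exception is made for a primary that grows while awaiting its planned resection.
- **Study design, Table 2.** Every patient enters with the tumour in place, since eligibility requires "Having measurable lesion on MRI axial section".
- **Interventions.** Arm A has three NAC courses, surgery, then two adjuvant (AC) courses. Arm B has surgery first, then three AC courses.
- **Participant timeline.** Treatment is to start within 7 days (arm A) or 28 days (arm B) of registration. In Table 3 the rows "MRI of primary site" and chest CT are marked before surgery in arm A. In arm B they are marked only at enrolment and follow-up.
- **Participant timeline, discontinuation text.** Disease exacerbation after NAC has started stops further chemotherapy, but: "In case of discontinuation of NAC, protocol treatment is continued, and surgery is performed after determining tumour reduction efficacy as far as possible". These patients then receive no AC.
- **Introduction.** In the earlier single-arm trial (JCOG0304), "the primary tumour became a progressive disease (PD) according to the revised Response Evaluation Criteria in Solid Tumours (RECIST) guidelines during NAC in 4.3" per cent of patients. In the later randomised trial (JCOG1306), "only 1.4% of the patients showed partial response (PR), whereas 8.6% presented PD during NAC".

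**The concern.** An arm A patient whose primary grows enough on NAC to meet RECIST progression becomes a PFS failure at that moment, although the protocol still takes the patient to resection. In arm B the primary is removed first. After that this type of event cannot occur, and before it no scan is scheduled that would find it. New lung lesions, too, have a scheduled CT before surgery in arm A only.

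The PFS comparison thus adds together two different things: growth of a tumour that is then resected, and relapse after resection. If relapse after resection and death were identical in the two arms, PFS could still look better in arm B. PFS is the first secondary endpoint listed, and a reader could take such a result as better disease control with immediate surgery.

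**Working it through.** **1. The plan's own figures.** The article gives no design figure for PFS. Its OS figures were checked only to confirm that they do not depend on PFS.
- Margin: ln(0.77)/ln(0.85) = 1.608, which agrees with 1.61.
- Events at one-sided 10% and 70% power (Schoenfeld): 4 × (1.282 + 0.524)² / (ln 1.61)² = 57.5.
- Event probability with exponential survival, 6 years of uniform accrual and 3 years of follow-up: 0.274. N = 57.5/0.274 ≈ 210, or 221 with an assumed 5% loss. Freedman's formula gives 218. The stated 224 is in line with these.

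None of these figures uses PFS.

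**2. Exposure to the event, side by side.**

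| | Arm A | Arm B |
|---|---|---|
| Time with the primary in place | Start within 7 days, then three NAC courses | Until surgery; treatment starts within 28 days |
| Scheduled MRI and chest CT before surgery (after enrolment) | Yes | No |
| Growth of the primary counts in PFS | Yes | Yes, but only in this short window |
| Surgery within protocol treatment after growth on NAC | Yes | Not applicable |

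**3. Expected number of such events in arm A.** 112 × 0.043 = 4.8 and 112 × 0.086 = 9.6, so about 5 to 10. The upper figure assumes that all of the 8.6% is growth of the primary.

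**4. Hand check with equal true outcomes.** Take 5-year PFS of 63.8% in both arms (JCOG0304, Introduction) and add independent growth on NAC in arm A.
- 4.3%: 0.638 × 0.957 = 0.611. Ratio of cumulative hazards (B/A) at 5 years: ln(0.638)/ln(0.611) = 0.91.
- 8.6%: 0.638 × 0.914 = 0.583. Ratio: ln(0.638)/ln(0.583) = 0.83.

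**5. Simulated Cox model.** Same 63.8%, exponential PFS, 6 + 3 years, progression on NAC at 0.15 to 0.30 years. The hazard ratio comes from 200,000 patients per arm. The last column comes from 2,000 trials of 112 per arm. The one-sided 10% level is borrowed from OS, because no PFS test is stated.

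| Progression on NAC | Relation to later relapse | HR (B/A) | Test favours B |
|---|---|---|---|
| None | – | 1.00 | about 10% |
| 4.3% | Unrelated | 0.91 | 22% |
| 8.6% | Unrelated | 0.82 | 37% |
| 4.3% | All would relapse within 5 years | 0.99 | 13% |
| 8.6% | All would relapse within 5 years | 0.95 | 13% |

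A second simulation used PFS of 73.5% at 4 years (JCOG1306, Table 1; there given at 46–48 months). It gave 0.88 and 0.83 if unrelated, and 1.00 and 0.97 if all these patients would have relapsed within 3 years.

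**6. An opposite effect.** Relapse after resection cannot precede resection, which comes later in arm A. If relapse hazard is assumed to start at surgery (week 12 in arm A, week 4 in arm B), the hazard ratios for 4.3% and 8.6% become about 0.93 and 0.82 if unrelated. They become 1.03 and 1.01 if all these patients would relapse within 3 years.

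**7. Possible share of PFS events.** In the JCOG1306 arm on this regimen, 0.086 × 70 = 6 patients progressed on NAC, against about (1 − 0.735) × 70 = 18.6 PFS events by 46–48 months. That is up to a third, on the same assumption as in step 3.

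**The case against.** The strongest reply is that growth on NAC is a real cost of giving chemotherapy first, and that PFS from enrolment by assigned strategy should count it. The documents lend this weight. A patient whose NAC is stopped loses the planned AC (Participant timeline), and three of 65 limb-sparing candidates (4.6%) in JCOG1306 had an amputation after NAC (Introduction). This stands: the present definition is a legitimate estimand, not an error.

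Several stronger inferences are tempting but lack support.
- *That the growing tumour is as curable as its arm B counterpart.* The lost AC and the possible larger surgery speak against this.
- *That PFS will be used to prop up the OS claim.* No section says so. Non-inferiority and the interim analyses rest on the primary aim (Sample size, Statistical analysis, Data collection), and the Discussions section draws no conclusion from PFS.
- *That the shift is always towards arm B.* Step 6 shows that later resection in arm A can cancel it when growth on NAC foreshadows early relapse.
- *That all of the 8.6% is growth of the primary.* The Introduction names the primary only for the 4.3%. Metastatic progression would remain an event under any sensible definition.

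Two cautions also stand. Blank cells in a condensed Table 3 are weak evidence: it shows no arm B body weight after enrolment either, and it does schedule a chest X-ray at each arm B AC course. Further, the discontinuation text lists progression of disease as a reason to end protocol treatment, next to the rule that takes patients with exacerbation on NAC to surgery. The reading here is that the NAC-specific rule governs growth on NAC.

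What the reply does not remove is that two unlike events are counted as one, with unequal time at risk and unequal scheduled imaging. Extended surgery, limb salvage and NAC response already have their own endpoints, so PFS need not be the only place where this cost shows.

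**Conclusion.** The point holds as a limitation on reading PFS between the arms. As defined, PFS contains an event to which arm A is exposed for three courses and arm B only briefly, and this tends to favour arm B. With equal true outcomes the PFS hazard ratio (B/A) is about 0.91 to 0.82 if growth on NAC is unrelated to later relapse, and close to 1.0 if these patients would have relapsed early anyway. The article gives no information on where in this range the truth lies.

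The figures assume exponential PFS, progression rates like those of the two earlier trials, early timing of progression, and that it is growth of the primary. The 63.8% may itself already include progression on NAC. OS, its sample size and the non-inferiority decision are unaffected. A reader might infer that the PFS definition is invalid and must be replaced. The documents do not support that; choosing between the two definitions is a choice of estimand.

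**What to change.** Keep the current PFS definition and prespecify a companion between-arm analysis beside it.

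- **Events in the companion analysis:** progression that prevents complete resection, macroscopically incomplete resection, distant metastasis, recurrence after resection, or death from any cause. Growth of a primary that is then completely resected is not an event; it stays in the NAC response endpoint.
- **Imaging check:** repeat the comparison with all pre-surgical and during-treatment events dated at one common landmark after enrolment, because scheduled imaging differs by arm.
- **Interpretation:** state in advance that a PFS advantage for arm B will not be interpreted without the companion analysis.

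The cost is endpoint wording and one extra analysis with its landmark check. Treatment, OS and sample size do not change. The companion version is less directly comparable with PFS in JCOG0304 and JCOG1306, but the retained definition keeps that link. Surgical margin is a planned subgroup factor, so it should be recorded. Whether completeness of resection and the site of each progression are also recorded should be confirmed against the case report form, which is not shown. If the full protocol or analysis plan already contains such an analysis, nothing more is needed than to cite it when PFS is reported.
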